## Results

Although the study was designed and Ethical Board Committee approval granted in the past, we have experienced difficulties in the phase of patient recruitment due to the outbreak of the novel coronavirus.

It is worth noting that the majority of tests are routinely performed in the diagnostic workup of patients with ILDs; therefore, patients will not be subjected to additional risks. Discomfort may be caused by the drawing of more blood samples than usual; however, this will be reduced by the use of vacuum blood collection systems.

This study will start recruiting patients to phase 1 in October 2023. The final results will be available in 2028. We plan to publish preliminary results after 2-3 years from the start of phase 1.

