**Methods:**

This multicenter prospective study plans to recruit 240 participants divided into 1 study group and 2 control groups. Biological fluid samples will be collected according to Polish Respiratory Society management guidelines and stored at –80°C for further tests. Prospective 5-year observations of 60 newly diagnosed individuals are planned. The study will be divided into subsections. First, we plan to characterize Polish patients with IPAF (study group) against their peers with other ILDs (2 control groups). Control group 1 will comprise patients with idiopathic ILDs, including mainly idiopathic pulmonary fibrosis and nonspecific interstitial pneumonia. Control group 2 will comprise patients with connective tissue disease–associated interstitial lung diseases, such as rheumatoid arthritis, systemic sclerosis, polymyositis, dermatomyositis, Sjögren’s syndrome, mixed connective tissue disease, and systemic lupus erythematosus. Radiological and functional parameters will be analyzed. Patients will be compared in terms of high-resolution computed tomography results, the 6-minute walking test performance, and pulmonary function test parameters. The diagnosis of IPAF will be reassessed on a regular basis through multidisciplinary discussion in order to determine its clinical stability. In the laboratory arm, inflammation and fibrosis pathways will be assessed. Cytokine levels (interleukin 8, transforming growth factor beta 1, chemokine C-C motif ligand [CXCL]18, CXCL1, surfactant protein [SP]-A, SP-D, Krebs von den Lungen-6 protein, and chitinase 1) will be measured in serum and BALF. A comparative analysis of serum and BALF cytokine levels will be performed in order to establish potential differences between systemic and local inflammatory pathways. In the quality of life (QoL) arm of the study, dyspnea and cough and their impact on various aspects of the QoL will be assessed. Depression and anxiety will be measured with the Hospital Anxiety and Depression Modified Scale and the 9-item Patient Health Questionnaire, and potential correlations with symptom prevalence will be assessed.

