## Methods

### Study Population

Inclusion criteria are as follows: individuals with ILDs, aged ≥18 years, and able to provide informed consent.

The study group will comprise patients with IPAF defined according to the criteria established by the Working Group of the ERS and the ATS [1]. Control group 1 will comprise patients with the following CTD-ILDs: rheumatoid arthritis (RA), systemic sclerosis (SSc), polymyositis (PM), dermatomyositis (DM), Sjögren’s syndrome (SS), mixed connective tissue disease (MCTD), and systemic lupus erythematosus (SLE) diagnosed according to the diagnostic criteria issued by the European League Against Rheumatism (EULAR) or the American College of Rheumatology (ACR). Control group 2 will comprise patients with the following IIPs: IPF, nonspecific interstitial pneumonia (NSIP), cryptogenic organizing pneumonia (COP), acute interstitial pneumonia (AIP), respiratory bronchiolitis–associated interstitial lung disease (RB-ILD), desquamative interstitial pneumonia (DIP), and lymphocytic interstitial pneumonia (LIP). Previously untreated patients with a new diagnosis of ILD were recruited for a pilot study (a separate population of patients) [7].

Exclusion criteria include age<18 years; respiratory tract infection, including minor upper respiratory tract infections (eg, the common cold) 4 weeks prior to the diagnostic process; asthma; tuberculosis; asbestosis; chronic hypersensitivity pneumonia; Hermansky-Pudlak syndrome; and other causes of genetic ILDs (eg, lymphangioleiomyomatosis, tuberous sclerosis complex [TSC], Birt-Hogg-Dubé syndrome, dyskeratosis congenita, familial forms of ILD, immunodeficiency syndromes); a history of therapy for ILD, including systemic glucocorticosteroids (GCs; both pulsed and long-term low-dose therapy); pregnancy and nursing; malignancy; HIV seropositivity; and a lack of ability to provide informed consent. For the QoL arm of the study, we will also exclude participants unable to communicate verbally.

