### Study Design

#### Phase 1

All patients meeting the inclusion criteria and not meeting the exclusion criteria regardless of prior treatment history will be recruited to phase 1 of the study. The recruitment process duration is estimated at 12 months. The previous recruitment of 40 patients led to a pilot study [7], which impacted further study design. The maximum number of patients included in this phase will be 80 (33.3%) in the IPAF group, 80 (33.3%) in the CTD-ILD group, and 80 (33.3%) in the IIP group.

#### Phase 2

Only patients with newly diagnosed disease (eg, no prior diagnosis of ILD and, hence, no prior treatment) will be recruited. The estimated recruitment duration is 36 months. The number of patients to be included in this phase will be 20 (33.3%) in the IPAF group, 20 (33.3%) in the CTD-ILD group (only those with RA, SSc, PM/DM), and 20 (33.3%) in the IIP group (only those with IPF, NSIP, COP, LIP; optimally 10, 50%, patients in the IPF subgroup and 10, 50%, in the non-IPF subgroup). Patients who were previously recruited to phase 1 of the study and meet the inclusion criteria of phase 2 may also be included.

Please see Figure 2 for a flowchart of the study design.

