**Figure 2 figure2:**
[figure not shown]
Flowchart of the study design. CTD-ILD: connective tissue disease–associated interstitial lung disease; IIP: idiopathic interstitial pneumonia; IPAF: interstitial pneumonia with autoimmune features; V: visit.

#### Visit 1

A thorough medical history will be obtained using the Visit 1 questionnaire. During the first hospitalization, the following procedures will be performed:

Pulmonary function tests (PFTs)Depression and anxiety assessmentBlood analysisFiberoptic bronchoscopy (FOB) with bronchoalveolar lavage (BAL) and bronchial mucosa samplingThe 6MWTComputed tomography (CT)Transthoracic echocardiography (TTE)

#### Visit 2

Only patients who qualify for phase 2 of the study will have further visits (60 newly diagnosed patients). The following procedures will be performed after an average of 6 (SD 3) months from visit 1:

The Visit 2 questionnaireCough assessmentDyspnea assessmentDepression and anxiety assessmentPFTs, the 6MWT, and oxygen saturation (SpO2) measurementArterial blood gas (ABG) analysis (if indicated)

#### Visit 3

The following procedures will be performed after an average of 12 (SD 3) months from visit 1:

The Visit 2 questionnaireCough assessmentDyspnea assessmentDepression and anxiety assessmentPFTs and the 6MWTHigh-resolution computed tomography (HRCT)Blood sampling (including testing for autoantibodies and potential biomarkers)FOB with BAL (optionally, if clinically indicated)Capillary blood gas (CBG) analysisTTERheumatological consultation

#### Visit 4

The following procedures will be performed after an average of 24 (SD 3) months from visit 1:

The Visit 2 questionnaireCough assessmentDyspnea assessmentDepression and anxiety assessmentPFTs and the 6MWTHRCT (if clinically indicated)Blood sampling (including testing for autoantibodies and potential biomarkers)FOB with BAL (if clinically indicated)CBG analysis

#### Visit 5

The following procedures will be performed after an average of 60 (SD 3) months from visit 1:

The Visit 2 questionnaireCough assessmentDyspnea assessmentDepression and anxiety assessmentPFTs and the 6MWTHRCT (if clinically indicated)Blood sampling (including testing for autoantibodies and potential biomarkers)FOB with BAL (if clinically indicated)CBG analysisRheumatological consultation

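### Final results are announced for 2028, but on the protocol's own estimates the last 60-month visit falls about October 2031, or October 2032 if phase 2 follows phase 1

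*Protocol article*

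**What the plan says.** The dates stand in the Results section and, in the same words, in the Results paragraph of the Abstract: "This study will start recruiting patients to phase 1 in October 2023", and "The final results will be available in 2028". Preliminary results are promised 2 to 3 years after the start of phase 1.

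The durations stand under Study Design. For phase 1: "The recruitment process duration is estimated at 12 months". For phase 2: "The estimated recruitment duration is 36 months". No start date is given for phase 2, but overlap between the phases is allowed: "Patients who were previously recruited to phase 1 of the study and meet the inclusion criteria of phase 2 may also be included".

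Only phase 2 patients have visits after visit 1. For visit 5: "The following procedures will be performed after an average of 60 (SD 3) months from visit 1". The Abstract's Methods paragraph says the same in other terms: "Prospective 5-year observations of 60 newly diagnosed individuals are planned".

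Two stated aims need those 60-month data. The Objectives section includes a 5-year assessment of whether the IPAF diagnosis is stable or progresses to another disease. The Discussion (Summary) plans to compare 1-, 3- and 5-year survival between RA and IPAF patients with a UIP pattern.

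**The concern.** A study that begins recruiting in October 2023 and follows its earliest patient for 60 months reaches that patient's last visit in October 2028. The year 2028 therefore fits only the first entrants. It leaves no room for the recruitment period, which the same article puts at 36 months for phase 2.

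At stake are the two aims that need complete 5-year follow-up. If the final analysis took place in 2028, most phase 2 patients would not have reached visit 5. The diagnostic status at 60 months would be unknown for them, and any 5-year survival estimate would rest on very few patients still at risk at that time.

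**Working it through.** **Inputs, all from the protocol article**
- Start of recruitment: October 2023 (Results).
- Phase 1 recruitment: 12 months, estimated (Study Design, Phase 1).
- Phase 2 recruitment: 36 months, estimated; 60 patients, 20 per group (Study Design, Phase 2).
- Visit 5: 60 months after visit 1, SD 3 (Study Design, Visit 5). I also show 57 and 63 months, reading the 3 months as a tolerance. That is an interpretation, because the article gives an average and an SD, not a window.

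**Assumptions, not in the article:** the phase 2 start date (October 2023 or October 2024) and uniform entry.

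**1. The stated year.** October 2023 + 60 months = October 2028. The year 2028 is reproduced only for a patient enrolled at the very start.

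**2. Last visit 5** = phase 2 start + recruitment duration + visit time.

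| Phase 2 start | Recruitment | Visit 5 at 57 mo | at 60 mo | at 63 mo |
|---|---|---|---|---|
| October 2023 | 36 mo | July 2031 | October 2031 | January 2032 |
| October 2024 | 36 mo | July 2032 | October 2032 | January 2033 |
| October 2023 | 12 mo (faster than stated) | July 2029 | October 2029 | January 2030 |

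None of these falls in 2028. Working backwards, 36 + 60 = 96 months before December 2028 is December 2020, so recruitment would have had to begin by then.

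**3. Patients with visit 5 by the end of 2028.** From 1 October 2023 to 31 December 2028 is 63 months. With uniform entry over 36 months from October 2023, n = 60 × (63 − v)/36, where v is the visit time in months:
- v = 60: 60 × 3/36 = 5 (8%)
- v = 57: 60 × 6/36 = 10 (17%)
- v = 63: 60 × 0/36 = 0

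If these are spread evenly over the three groups, that is 5/3 ≈ 1.7 patients per group of 20, and at most 10/3 ≈ 3.3.

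With phase 2 starting in October 2024 and nobody carried over from phase 1, the longest possible follow-up is 63 − 12 = 51 months, so n = 0.

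With all 60 entered within 12 months from October 2023: 60 × 3/12 = 15 at v = 60, and 60 × 6/12 = 30 at v = 57.

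**4. What is not affected.** If the phases start together, the last patient enters about October 2026 and reaches 24 months about October 2028, so visits 2 to 4 can be complete by the end of 2028. With a sequential start, the last 24-month visit would be about October 2027 + 24 months = October 2029. The phase 1 comparisons need only visit 1.

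**The case against.** Several points on the other side have weight.

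- **The durations are estimates.** Recruitment could run faster, so it would be too strong to infer that the study cannot finish before late 2031. That stands, and July 2031 is already possible at 57 months. But faster recruitment does not rescue 2028: even 12-month entry ends about October 2029, or July 2029 at 57 months.
- **Carry-over from phase 1 is allowed.** A reader might infer that a sequential start leaves no patient at all with visit 5 by the end of 2028. That holds only without carry-over, since visits are counted from visit 1 and a carried-over patient could have had visit 1 as early as October 2023. The October 2031 date already allows for this, because it assumes that entry begins in October 2023.
- **The accrual pattern is unknown.** The count of 5 of 60 depends on uniform entry. Front-loaded entry would raise it.
- **No 2028 data cut-off is fixed.** A reader might infer that the authors intend to present heavily censored data as the 5-year result. The article does not say so. The authors may simply have added five years to the start date and may analyse only when follow-up ends. In that case the error lies in the announced date, not in an analysis rule.
- **Other results are safe.** The Objectives section names the incidence of IPAF as the primary purpose, and this does not depend on visit 5.

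Two possible rescues fail. The pilot patients give no earlier start, because the Study Population section calls them "a separate population of patients". Nor does the article say that the final results cover phase 1 alone: it contrasts them with preliminary results after 2 to 3 years and sets no other end point.

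**Conclusion.** The point holds as an inconsistency between the announced date and the stated durations. On the protocol's own estimates, final results in 2028 are about 3 years too early if the phases start together and about 4 years too early if they are sequential. This rests only on dates and durations in the article, with the phase 2 start date as the one open input. No variant examined brings the last visit 5 into 2028.

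The consequence for the data is conditional. If 2028 were used as the final analysis, about 5 of 60 patients (0 to 10) would have visit 5 under uniform entry from October 2023, and 5-year diagnostic stability and 5-year survival could not be delivered. The documents do not show that such an analysis is planned.

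**What to change.** In both the Abstract (Results) and the Results section:

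1. State when phase 2 recruitment starts.
2. Restate the final results as following the last patient's visit 5. On the stated estimates this means late 2031 to 2032 if the phases start together, and late 2032 to 2033 if phase 2 follows phase 1.
3. Label any 2028 report as interim.
4. Make 5-year claims (diagnostic stability, 5-year survival) only from the final analysis.

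The change takes a few sentences and leaves the design, sample and tests as they are. Its cost is that the announced final date becomes later.

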## Discussion

### Summary

As IPAF is an exclusion diagnosis, we believe that in the era of genetic testing advancements, genetic disorders manifesting as ILDs should be considered as alternative etiologies. In our study, the local bioethics committee granted permission to perform genetic testing, and we plan to bank full blood, with the intention to perform such procedures.

There have been clinical reports of individuals with signal transducer and activator of transcription 3 (STAT3) gain-of-function syndrome [49] or cytotoxic T cell antigen 4 (CTL-A4) checkpoint haploinsufficiency [50], which could fulfill the 2015 criteria. Moreover, a newly discovered coatomer protein complex subunit alpha (COPA) syndrome causes progressive ILD [51]. The impaired COPA protein may contribute to endoplasmic reticulum stress and therefore trigger interferon signaling pathways and T cell–mediated inflammation [51].

Newton et al [52] revealed that the leukocyte telomere length is longer in individuals with IPAF and CTD-ILD than in those with IPF. The telomere length correlates with lung function and lung transplant outcomes in IPAF. Moreover, mucin 5B (MUC5B) and Toll-interacting protein (TOLLIP) polymorphisms are associated with both IPAF and IPF, which suggests that these 2 clinical entities have similar genetic backgrounds. Various polymorphisms are found in CTDs, such as RA, SS, and SSc, but to date, there are no data on whether the presence of these polymorphisms is associated with the development of IPAF. Hopefully, an in-depth understanding of molecular pathways could lead to the development of targeted therapies.

A practical question we are going to face stems from the fact that instructions for most ELISA kits that are available for research use in our area only contain suggestions/guidelines for serum dilution. Therefore, we will need to either predict the levels of the aforementioned proteins in BALF or experiment with dilution. As we are unsure how much time it will take to recruit the adequate number of individuals, we plan to perform a miniexperiment beforehand: First, we will test the serum according to the manufacturer’s guidelines. If the standard 1:40 dilution does not lead to the detection of predicted concentrations, we will check the 1:20 dilution, 1:5 dilution, and undiluted samples. The next step will be testing BAL samples. We will test 1:20 dilution samples, and again, if this does not result in the detection of protein concentrations within the range provided in the kit instruction, we will test the 1:5 dilution and undiluted specimens.

The clinical stability of IPAF is an important subject, as the development of mild extrapulmonary symptoms may be overlooked. In our opinion, this specific population requires above-average clinical vigilance due to the fact that reclassification as definite CTD-ILD prompts a change in the therapeutic approach based on ACR/EULAR guidelines. This is why we plan to cooperate closely with rheumatologists regarding assessment of the extrapulmonary manifestations of autoimmunity. However, there is also a possibility that an entity that had been initially classified as idiopathic ILD may later be reclassified as IPAF. To test this hypothesis, we plan periodic rheumatological revaluations of this subgroup, together with retesting for ANAs (serological domain of IPAF).

Data on the progression of IPAF to CTDs are scarce and conflicting. Scirè et al [53] reported that 42% of patients with IPAF with antisynthetase antibody positivity were ultimately reclassified as RA-ILD, PM/DM-ILD, or myositis-RA overlap syndrome. Ito et al [54] also reported that 12.2% of individuals meeting IPAF serological and morphological criteria were diagnosed with CTD during a median follow-up period of 54 months. However, Chartrand et al [55] found that none of the 56 individuals with IPAF was rediagnosed over a follow-up period of 48 months.

Another question is when to initiate treatment during the course of IPAF. Before IPAF was defined, ILD with symptoms of underlying autoimmune disorder but without extrapulmonary manifestation could have been classified as IIP and therefore have delayed treatment initiation. In our prospective observational study, we will surely face a challenge in identifying patients with IPAF who require early clinical intervention. We hope that during the 60-month observation period, we will be able to identify molecular, radiological, and functional prognostic factors, which, in the future, will help lay the foundation for IPAF therapy guidelines.

In a study on 412 patients with CTD-ILD or IPAF, Li et al [56] analyzed the relationship between these 2 entities in order to identify which individuals with IPAF should commence treatment early. They concluded that based on similar yet milder symptoms and ANA positivity, IPAF is in fact an early stage of CTD-ILD and therefore treatment should commence early. After immunosuppressive treatment, they reported an increase in the FVC and DLCO in this population. The choice of adequate pharmacotherapy is another clinical question that we will face during prospective observation.

D’Silva et al [57] presented a case series of 50 patients from 2 centers who were treated with rituximab (RTX). The majority experienced either clinical improvement or stability understood as global assessment of performance in terms of oxygen requirement, unplanned hospitalization due to respiratory reasons, and 1-year survival, despite baseline differences regarding age, comorbidities, and prior treatment history.

Although we do not plan a randomized controlled trial, in prospective observation, we will face clinical decisions regarding treatment implementation. We hypothesize that some patients will have a history of treatment with systemic GCs or cyclophosphamide (CYC), and we wonder whether the results of studies on CTD-ILDs can be extrapolated to the IPAF population. The use of CYC is associated with an increased risk of malignancy, infections, and bone marrow suppression [58].

Some patients in this study had previously used mycophenolate mofetil (MMF) or tacrolimus, which may have impacted their performance on RTX. The implementation of RTX therapy, especially in patients with refractory ILD, should be considered due to its favorable safety profile [59]. We also hypothesize that a usual interstitial pneumonia (UIP) radiological pattern, which is associated with higher mortality in patients with IPAF [60], may impact treatment efficacy.

We wonder whether studies on patients with RA-ILD who generally have a UIP pattern may be extrapolated to this specific IPAF population, and in prospective observation, we plan to exteriorize 2 subpopulations (UIP-RA and UIP-IPAF) and compare patients’ outcomes in terms of oxygen requirement, PFT results, 6MWT performance, and 1-, 3-, and 5-year survival.

We are looking forward to cooperating with rheumatologists for multidisciplinary discussion.

### Impact of Pilot Study Results on the Protocol

In our pilot study [7], we revealed a greater prevalence of gastrointestinal reflux disease (GERD) in the CTD-ILD group than in the IPAF and IIP groups. Data on the impact of GERD on fibrosis pathogenesis are conflicting. There are data suggesting that exposure of the interstitial tissue to a low pH results in repeated lesions and, consequently, progressive fibrosis. However, there are also data supporting a hypothesis that GERD actually results from progressive fibrosis and a shift in intrathoracic pressure due to altered anatomy. Therefore, we decided to launch a substudy on patients with progressive fibrosing ILD (PF-ILD), focusing on the impact of GERD on the disease course. We will monitor 24-hour impedance-pH to objectify GERD episodes and correlate them with symptoms.

In the pilot study [7], it was also revealed that BALF levels of interleukin 8 (IL-8), CXCL1, and TGF-β1 were significantly higher in the CTD-ILD group than in the IPAF and IIP groups. We hope that the analysis of 240 subjects in this full-size study will reveal more defined differences between study groups. We plan to analyze subgroups (eg, RA-ILD or SSc-ILD) and compare them with their IPAF counterparts (based on the presence of clinical symptoms and specific autoantibodies). We also plan to distinguish an IPAF subgroup associated with the presence of antisynthetase autoantibodies and compare it with the PM/DM-ILD subgroup in terms of clinical stability and outcomes.

Our pilot study [7] also revealed that the BALF IL-8 concentration is associated with the presence of skin teleangiectasias. IL-8 is a known proangiogenic factor. In this full-size study, we plan to perform videocapillaroscopy to stratify participants according to the Cutolo nailfold capillaroscopy classification and measure the concentration of proangiogenic cytokines in both serum and BALF. We will be able to compare corresponding Cutolo subgroups of SSc-ILD and IPAF and determine the impact of proangiogenic factors on pathological angiogenesis.

We also hypothesize that there will be significant intergroup differences between the reported severity of cough and dyspnea as well as psychological symptoms and their impact on various aspects of the QoL.

